### Internal pilot study

A 6-month internal pilot phase was conducted at three breast cancer units (Coventry, Oxford and Wolverhampton) to evaluate processes for patient identification, eligibility and refinement of recruitment estimates. The intended sample size for the internal pilot study was 30 participants, approximately 10% of the full sample. Acceptability of the PROSPER intervention was explored through qualitative research involving audio-recorded individual interviews with seven participants. Changes were made to patient-facing materials and to exercise intervention materials. Easy-to-use pocket-sized laminated cards with details of inclusion/exclusion criteria and shoulder screening criteria were produced for recruitment staff. Additional telephone or face-to-face appointments were added to the exercise intervention to allow for flexibility during ongoing cancer treatment. Data from the pilot phase helped to refine recruitment and trial processes. Patients recruited to the pilot phase continue with the follow-up schedule and will be retained in the full trial analysis. The pilot study was completed as planned and the funder approved progression to full trial.

### Data analysis

Statistical analysis will be intention-to-treat and will comply with the Consolidated Standards of Reporting Trials (CONSORT) guidelines. The primary outcome data will be summarised using mean, SD, median and range values. The clustering effect will be assessed prior to analysis of the data. In the presence of a clustering effect, the primary outcome will be analysed using multilevel linear regression models. If there is negligible clustering effect, it will be analysed using ordinary linear regression models. In each case, the mean change from baseline (to 6 and 12 months) will be summarised for each of the treatment arms and differences between the interventions using unadjusted and adjusted (for age, type of surgery and RT) estimates. These mean changes and their 95% CIs will be plotted graphically so that change can be assessed over the course of the study. Continuous secondary outcomes will be assessed in a similar way to the primary outcome. Categorical data will be analysed using random effect/ordinary logistic models, depending on the presence of a clustering effect.

A DASH score cannot be computed if there are more than three missing items. As a sensitivity analysis, the impact of missing data will be assessed using multiple imputation. The impact of non-compliance with the intervention will be examined using the complier average causal effect (CACE) analysis.^20 21^ We have reviewed definitions of compliance for CACE analyses used in other therapy trials.^22 23^ Complete compliance with the PROSPER intervention is defined as having three or more contacts with the PROSPER therapist; an additional analysis will be undertaken to explore partial compliance, defined as less than three sessions. Analyses and template tables will be reported in a detailed statistical analysis plan for review and approval by the Data Monitoring Committee (DMC), prior to final statistical analysis of the data. Planned sensitivity analyses include: a) the impact of low/high recruitment centres on clustering effect and b) assessment of differences between date of randomisation and date of surgery across groups, as surgical trials vary in relation to timing of follow-up.

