## Sample size

PROSPER aims to recruit 350 patients, allocated in a 1:1 ratio. The sample size calculation is based on a Dutch trial of 30 women with breast cancer, randomised to physiotherapy over a 3-month period, reporting a between-group difference of 7 points on the DASH at 6 months.^18^ At 80% power and P<0.05, this yields a target of 242 participants in total. Accounting for therapist effects, an intracluster coefficient (ICC) of 0.01 (yielding a design effect of 1.05), gives a target of 256 participants. The ICC estimate is based on our previous experience of exercise interventions in a range of musculoskeletal trials. We anticipate loss to follow-up of <10% based on our previous clinical trials however, have inflated this to 25% to cover the possibility that numbers lost to follow-up are greater than anticipated, for example, due to ongoing cancer treatment.

The study is powered to detect a 7-point difference on the DASH. Studies of rheumatological and orthopaedic populations have suggested that the minimally clinically important difference for the DASH is 10, and that the between-group difference for trials should be set at 10.^19^ However, this fails to account for many of the eventualities that occur in pragmatic trials, notably that there is not a ‘no treatment’ control arm, and therefore that some of the control group may be exposed by serendipity to an intervention of similar intensity, particularly in a high-risk population.

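### The sample size assumes therapist clustering, but the primary model keeps it only if a look at the trial data finds it, by a criterion the article does not state

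*Protocol article*

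**What the plan says.** In the Protocol article, Sample size, clustering by therapist is part of the design: "Accounting for therapist effects, an intracluster coefficient (ICC) of 0.01 (yielding a design effect of 1.05), gives a target of 256 participants". The starting figure is 242 ("At 80% power and P<0.05, this yields a target of 242 participants in total").

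Under Data analysis, the same clustering becomes conditional. First, "The clustering effect will be assessed prior to analysis of the data". A multilevel linear regression follows if clustering is found. Otherwise, "If there is negligible clustering effect, it will be analysed using ordinary linear regression models". Continuous secondary outcomes are handled like the primary outcome, and the logistic models for categorical outcomes carry the same condition.

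The section does not say what counts as negligible or whether the assessment is a significance test. It also does not say whether the cluster is the therapist or the centre. The only unit it mentions is the centre, in a planned sensitivity analysis on low and high recruiting centres.

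**The concern.** The two sections do not fit together. The design treats therapist clustering as expected, on the strength of the team's own earlier trials, and pays for it in recruitment. The analysis may then drop it because the data did not show it. Failure to find a small ICC in a trial of this size is weak evidence that it is absent.

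Two things are at stake. The primary model is not fixed in advance, because it depends on outcome data. And if real clustering is missed, ordinary regression gives a standard error that is too small and a confidence interval that is too narrow.

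**Working it through.** **Inputs from the Protocol article.** Sample size: 7 DASH points, 80% power, P<0.05 (two-sided assumed), 242 before inflation, ICC 0.01, design effect 1.05, 256 after clustering, 25% loss, 350 recruited 1:1. Trial design and setting: 17 centres. Interventions: a trial physiotherapist sees exercise-arm women only.

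**The plan's own figures.**
- 242 × 1.05 = 254.1, i.e. 255, against 256 stated.
- 256 / 0.75 = 341.3, i.e. 342, against 350 stated. Both agree within 3%.
- The SD behind 242 is not stated. An SD of about 19.4 reproduces 242, so that step is back-solved and not independently checked.
- 1 + (m − 1) × 0.01 = 1.05 gives m = 6 women per therapist.

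**Assumed layouts.** The number of therapists is not given. With 256 / 2 = 128 analysed in the exercise arm, 6 women each means about 21 therapists. A layout of 10 therapists with 13 women each shows the effect of larger caseloads.

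**How often clustering would be found.** For k therapists with m women each and ICC ρ, the power of the one-way random-effects F test is P(F > Fcrit / (1 + mρ/(1 − ρ))), with k − 1 and k(m − 1) degrees of freedom. The divisor for 21 × 6 is 1 + 0.06/0.99 = 1.061 at ICC 0.01 and 1 + 0.30/0.95 = 1.316 at ICC 0.05. The ANOVA estimate of the ICC is above zero exactly when F > 1, which gives the last column.

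| Layout | ICC | Found by 5% test | Missed if the rule is estimate > 0 |
|---|---|---|---|
| 21 × 6 | 0.01 | 7.3% | 46% |
| 10 × 13 | 0.01 | 8.9% | 46% |
| 21 × 6 | 0.05 | 21.6% | 25% |
| 10 × 13 | 0.05 | 32.5% | 20% |

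A laxer test helps only partly: for 21 × 6 at ICC 0.01, detection is 13.6% at the 10% level and 25.4% at the 20% level.

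**What ordinary regression loses.** With clustering in one arm only, the variance of the difference is multiplied by (1 + DE)/2, where DE = 1 + (m − 1)ρ. The true SE exceeds the reported SE by the square root of that factor.

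| Layout | ICC | DE | (1 + DE)/2 | SE ratio |
|---|---|---|---|---|
| 21 × 6 | 0.01 | 1.05 | 1.025 | 1.01 |
| 10 × 13 | 0.01 | 1.12 | 1.06 | 1.03 |
| 21 × 6 | 0.05 | 1.25 | 1.125 | 1.06 |
| 10 × 13 | 0.05 | 1.60 | 1.30 | 1.14 |

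**Type I error (simulated, exercise arm clustered).** A rule that uses a 5% test and then picks the model gives about 5% at ICC 0.01 and about 5.7-6.5% at ICC 0.05. Always modelling the clustering gives about 5.0-5.2%. With the estimate-above-zero rule, type I error stays at or below 5% at both ICCs.

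**The case against.** The strongest defence is that the article says clustering is assessed, not tested. A reader might infer that clustering will usually be ignored. That follows only under a significance test, which the article does not mention. Under an estimate-above-zero rule, clustering at the planned ICC is missed about half the time and type I error is not inflated. This stands, so the detection rates above are conditional on the rule.

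Second, at the only ICC the article gives, the numerical harm is trivial. An ICC of 0.01 with six women per therapist may be just what the authors mean by negligible. This also stands. An ICC of 0.05 is an assumption, five times the planning value.

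Third, the cluster under Data analysis may be the centre. Centres span both arms and stratify the randomisation, so leaving them out would tend to make the SE too large, not too small. The Sample size section points to the therapist ("Accounting for therapist effects"), but the ambiguity is real and is itself a reason to name the unit.

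Fourth, a reader might infer that the multilevel model would wrongly put the same therapist effect in both arms. The article does not say so. The random-effects structure and the degrees-of-freedom method are ordinary content for the analysis plan, and their absence here is no fault.

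The defence does not remove the conditional rule. An analysis plan could define negligible, but the primary model would still be selected from the data.

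**Conclusion.** The point holds in a limited form. The article states a data-dependent choice of primary model that is at odds with its own sample size assumption. The main fault is that the model is not fixed; the expected numerical harm is small.

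At the planned ICC of 0.01 the SE is about 1-3% too small under ordinary regression, and type I error is about 5%. The effect becomes noticeable only at an assumed ICC near 0.05 under a test-based rule. There the SE shortfall is about 6-14% when ordinary regression is used, and the overall type I error is about 5.7-6.5%.

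These sizes rest on 10 to 21 therapists, equal caseloads, therapist as the cluster, and clustering in the exercise arm only. A reader might conclude that the trial's error rate is seriously compromised; the documents do not support that. This is a change worth making before the data are seen, not a flaw that invalidates the design.

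**What to change.** Drop the preliminary check. Prespecify one primary model that keeps a therapist effect whatever the estimated ICC, and recognise that therapists treat only the exercise arm. Name the cluster unit. Report the ICC with its confidence interval. Use ordinary regression only as a sensitivity analysis or if the model does not converge. Apply the same rule to the continuous secondary outcomes and the logistic models.

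The cost is a change of wording, a slightly wider confidence interval, and a therapist identifier for each exercise-arm participant, with a coding rule for women who attend no session or see more than one physiotherapist. No extra recruitment is needed, because the target of 256 already allows for the planned therapist effect.

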### Eligibility criteria

Women are eligible to participate in PROSPER if they are: diagnosed with histologically confirmed invasive or non-invasive primary breast cancer scheduled for surgical excision; aged 18 years or over; can comply with the protocol; willing to provide written informed consent and considered as being at high risk of developing postoperative shoulder problems (table 2). This is a pragmatic trial and it is important that inclusion criteria reflect contemporary clinical practice. Therefore, women are also eligible where a later decision is made for postoperative RT to the axilla and/or supraclavicular region, thus changing their risk status from low to high. ‘Late entry’ women are eligible for the trial if the decision for postoperative RT is made within 6 weeks of surgery. Women who have had previous breast surgery (such as excision of a benign tumour or breast cyst) and those women who have had previous contralateral (opposite side) mastectomy, are eligible for invitation providing they fulfil high-risk criteria for shoulder problems. Women having immediate reconstruction or bilateral breast surgery are ineligible as the usual NHS postoperative care pathway often includes routine postoperative physiotherapy. Exclusion criteria are presented in table 2.

**Table 2 T2:** Trial inclusion and exclusion criteria

Inclusion criteria	Exclusion criteria
Age ≥18 years	Males
Histologically confirmed invasive or non-invasive primary breast cancer scheduled for surgical excision of breast cancer	Women having immediate reconstructive surgery
Considered high risk of developing shoulder problems after surgery defined by one or more of the following: Planned axillary node clearance Planned radiotherapy to the axilla and/or supraclavicular* Existing shoulder problems (based on PROSPER screening criteria)	Women having SLNB, with or without breast surgery, unless they fulfil other high-risk criteria
Obesity defined as body mass index >30	Women having bilateral breast surgery
Any subsequent axillary surgery related to primary surgery, eg, axillary lymph node clearance conducted after SLNB	Evidence of metastatic disease at time of recruitment
Able to provide written informed consent	
Willing and able to comply with the protocol	

*Includes women informed of need for radiotherapy to the axilla and/or supraclavicular within 6 weeks of surgery, thus potential late entry to the trial is allowed in this setting.

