### Allocation sequence generation and randomisation

Randomisation is based on a computer-generated algorithm held and controlled centrally by the Warwick Clinical Trials Unit (WCTU) programming team, independent from the PROSPER team. The WCTU telephone randomisation service is used whereby randomisation occurs after eligibility and informed consent has been obtained. Concealment of allocation is maintained. An automated confirmation email of intervention allocation is generated to the study team. Randomisation is stratified by the following variables: (i) first versus repeat surgery; (ii) centre and (iii) whether informed of the need for RT within 6 weeks of surgery. The first variable adjusts for the requirement for any additional surgery which may change risk status from low to high (eg, second procedure ANC or re-excision of surgical margins). The second stratification variable ensures balanced allocation across each recruitment site. The third variable accounts for late entry to the trial, thus relates to the timing of intervention delivery and whether participants are randomised preoperatively (up to the day of surgery) or within the first 6 weeks postoperatively. Due to the nature of the study intervention, it is not possible to blind participants or treating physiotherapists to treatment allocation. However, receipt and handling of outcome data collection is blinded, thus data entry of returned postal questionnaires, data cleaning and interim statistical analyses are conducted without knowledge of treatment allocation (blinded).

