## Outcomes

Figure 1 and table 3 present the study outcome measures and standardised assessment scales by assessment time point. Questionnaires are completed at baseline on recruitment, then at 6 weeks, 6 and 12 months after randomisation by post. The primary outcome is upper limb function at 12 months measured using the Disabilities of Arm, Shoulder and Hand (DASH) questionnaire.^14^ We considered other patient-reported outcome measures, including shoulder-specific scales, however selected the DASH because it captures symptoms and function of the upper limb rather than the shoulder joint per se. There is good evidence to suggest that women experience a variety of difficulties and restrictions after breast cancer treatment, affecting the hand, arm and shoulder. Functional impairment to the arm can affect performance of simple daily activities, including writing, opening or closing jars, lifting and/or holding shopping bags.

**Table 3 T3:** Outcome assessment

Outcome	Domain	Scale/measure	T_0_ baseline	t_1_ 6 weeks	t_2_ 6 months	t_3_ 12 months
Primary	Function	DASH				√
Secondary	Function	DASH subscales	√		√	√
	Acute and chronic pain Neuropathic pain	FACT-B4; NRS DN4	√ √	√ √	√ √	√ √
	Complications	SSI+self-report		√	√	√
	Lymphoedema	Self-report	√	√	√	√
	Health-related QoL	SF12/EQ-5D-5L	√		√	√
	Resource use	Self-report			√	√
	General activity and exercise	PASE items	√	√	√	√

DASH, Disabilities of Arm, Shoulder and Hand questionnaire; DN4, Doleur Neuropathique; EQ-5D-5L, Euroqol; FACT-B4, Functional Assessment of Cancer Therapy-Breast; NRS, numerical rating scale; PASE, Physical Activity Scale for the Elderly; QoL, quality of life; SF12, Short Form-12; SSI, surgical site infection; t, time point.

The DASH is a 30-item patient-reported outcome measure designed to capture difficulty in performing various upper arm activities.^14 15^ A single DASH score is generated, although psychometric assessment using discriminant content validation analysis has shown that the scale can be used to produce three health outcome subscores for impairment, activity limitation and participation restriction, as per the WHO International Classification of Functioning Disability and Health taxonomy.^16^

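### Mean change from baseline is pooled over preoperative and early postoperative baselines, which can shift the within-arm changes towards improvement; the between-arm difference is not biased

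*Protocol article*

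**What the plan says.** Four parts of the protocol article bear on this.

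- **Outcomes** ties baseline to recruitment, not to surgery: "Questionnaires are completed at baseline on recruitment, then at 6 weeks, 6 and 12 months after randomisation by post".
- **Eligibility criteria** admits a late-entry group: "women are eligible for the trial if the decision for postoperative RT is made within 6 weeks of surgery".
- **Allocation sequence generation and randomisation** stratifies on this, listing as its third factor "iii) whether informed of the need for RT within 6 weeks of surgery". It explains that the factor reflects "whether participants are randomised preoperatively (up to the day of surgery) or within the first 6 weeks postoperatively". Its first factor, first versus repeat surgery, covers women who need a further operation, such as "second procedure ANC or re-excision of surgical margins".
- **Data analysis** gives one rule for all women: "the mean change from baseline (to 6 and 12 months) will be summarised for each of the treatment arms". It reports "differences between the interventions using unadjusted and adjusted (for age, type of surgery and RT) estimates" and adds: "These mean changes and their 95% CIs will be plotted graphically so that change can be assessed over the course of the study". The same approach carries over to secondary outcomes that are continuous. Late entry and baseline DASH are not in the adjustment list.

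The second planned sensitivity analysis looks at the interval between randomisation and surgery across groups. As described, it neither redefines baseline nor splits the change.

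**The concern.** The change score means different things for the two entry groups. For a woman randomised before a first operation, it measures how far her function at 6 or 12 months differs from her function before treatment. For a late-entry woman, it measures how far she has moved from her state in the weeks after surgery, so it includes recovery from the operation. Table 1 gives the trial's primary purpose as prevention, and readers will naturally take the plotted changes as loss of function after treatment. A pooled mean describes neither group.

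What is at stake is the reading of the within-arm changes and their confidence intervals and, if the arms are compared on change, some precision. Adjusting for RT does not separate the groups, because planned axillary or supraclavicular RT is also an entry criterion for women randomised before surgery. Nor can the groups be put on a common reference later: Table 3 schedules no DASH at 6 weeks, so women randomised before surgery have no early postoperative score.

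**Working it through.** **Inputs from the article (Sample size):** difference 7 points, 80% power, P<0.05 (taken as two-sided), 242 in total, design effect 1.05, 256 after clustering, 25% loss, target 350. No SD is stated.

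**Reproducing the plan's figures**

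- Implied SD = 7 × √(121/2) / (1.960 + 0.842) ≈ 19.4, and this SD returns 121 per arm, 242 in total.
- 242 × 1.05 = 254.1, against 256 stated.
- 256 / 0.75 = 341.3, so 342, against 350 stated.
- Analysed number: 350 × 0.75 = 262.5, taken as 262 (131 per arm).

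The figures reproduce within 3%, and the point does not depend on them.

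**Assumed, because the article gives no values:** late-entry share f = 10–30%; rise D in DASH from before surgery to late-entry baseline = 10–20 points (higher meaning worse); correlation of baseline with 12-month DASH 0.5 for a preoperative and 0.3 for a postoperative baseline.

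**Step 1: shift in the pooled within-arm change.** Let R be the mean worsening from before surgery to 12 months, taken as equal in both groups. Preoperative entrants score R and late entrants R − D, so the pooled change is (1 − f)R + f(R − D) = R − fD.

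| f | fD at D = 10 | fD at D = 20 |
|---|---|---|
| 10% | 1 | 2 |
| 20% | 2 | 4 |
| 30% | 3 | 6 |

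Example: with R = 5 and D = 15, preoperative entrants average +5 (worse) and late entrants −10 (better). The pooled change is 3.5, 2.0 and 0.5 at f = 10%, 20% and 30%. The signs differ only when 0 < R < D.

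**Step 2: between-arm difference.** The shift fD is the same in both arms when late entry is balanced, and it cancels. A simulation stratified by entry (262 women, SD 19.43, true effect −7, f = 0–20%, rise 15 or 25) gave control-arm mean changes falling from 8.0 to between 6.5 and 3.0. The between-arm difference stayed at about −7.0 by change score, by 12-month score and with baseline adjustment.

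**Step 3: standard error of a change-score comparison.** The variance of change is 2 × 19.4² × (1 − 0.5) = 376.4 for preoperative and 2 × 19.4² × (1 − 0.3) = 526.9 for late entrants. Pooling the groups adds f(1 − f)D². SE = √(2 × variance / 131).

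| f, D | Variance within groups | Added | SE, groups separated | SE, pooled | Increase |
|---|---|---|---|---|---|
| 10%, 10 | 391.4 | 9 | 2.44 | 2.47 | about 1% |
| 20%, 20 | 406.5 | 64 | 2.49 | 2.68 | about 8% |
| 30%, 20 | 421.5 | 84 | 2.54 | 2.78 | about 10% |

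Within-arm confidence intervals for the pooled change widen in the same proportion. The pooled SE is the one an analysis without the stratum would report. With late entry balanced by the stratification, the estimate itself does not become more variable: in the Step 2 simulation its spread stayed at 2.36 to 2.44 throughout. The cost is an overstated SE. In the worst row, power for 7 points falls from about 79% to Φ[(7 − 1.96 × 2.78)/2.54], about 73%.

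**Step 4: if 12-month DASH is the modelled outcome.** SE = 19.4 × √(2/131) = 2.40 and power is about 83%. D does not enter.

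**The case against.** The strongest reply is that the trial's answer is untouched. This is a two-arm superiority trial with DASH at 12 months as the primary outcome, and late entry is a stratification factor. A reader might infer from the mixed baselines that the treatment effect is biased. The documents do not support that, and Steps 1 and 2 show why. Nor should the 1 to 6 points be set against the 7-point target: the target is a difference between arms, and the shift is common to both.

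A reader might also infer a material loss of power. That needs f = 30% and D = 20 together, and an analysis of change scores. The article is ambiguous here: it says the primary outcome will be modelled, then describes differences in terms of change. If 12-month DASH is modelled, little or none of the loss applies. RT adjustment would also absorb part of the spread.

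It is tempting to say that one woman would count as worsened or improved purely by when she entered. That is a counterfactual. Late entrants are a different group, initially judged low risk, and the signs differ only if 0 < R < D.

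Finally, the article defers detailed analyses and template tables to a statistical analysis plan, which may split by entry. If so, the point is met. But the published text is not silent: it fixes a single change per arm, a plot of it and an adjustment list without late entry. That much of the concern stands.

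**Conclusion.** The concern holds for the within-arm changes. As written, the plan averages changes from preoperative and early postoperative baselines under one label. If DASH is worse in the weeks after surgery than before, the pooled change is shifted towards improvement by fD, or 1 to 6 points under the assumed ranges. The direction rests on that assumption and the size on the late-entry share, neither of which the article gives; with few late entrants the shift is small. Validity of the between-arm comparison is not in question. The reported standard error of a change-score comparison would be about 1% to 10% too large if the stratum is left out. The case for changing the plan rests on interpretation more than on power. The reference-point problem is also slightly wider than late entry, because repeat-surgery women can be randomised before a second operation with a baseline that already follows the first.

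**What to change.** In the Data analysis section, and in the statistical analysis plan:

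1. Include the late-entry stratification factor, with baseline DASH, in the primary model. Do the same in the models for continuous secondary outcomes, with each outcome's own baseline where one is collected.
2. Summarise and plot change from baseline separately by entry timing, using the indicator already held for randomisation. Identify repeat-surgery women whose baseline follows an earlier operation, and do not label that baseline preoperative.
3. Where arms are shown with entry groups pooled, plot mean DASH at 6 and 12 months after randomisation, and note that time since surgery differs by entry group.

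The cost is revised wording and an extra split in tables and plots, with no new data, visits or patients. The late-entry panel will be small, with wide confidence intervals.

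### The between-arm difference on the primary outcome is described as change from baseline, and the covariate list omits baseline DASH, which costs precision and possibly power

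*Protocol article*

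**What the plan says.** The Outcomes section of the protocol article fixes the endpoint as a final score: "The primary outcome is upper limb function at 12 months measured using the Disabilities of Arm, Shoulder and Hand (DASH) questionnaire". Under Data analysis, if clustering is found, "the primary outcome will be analysed using multilevel linear regression models"; otherwise ordinary linear regression is used. The next sentence applies to both models. It says that "the mean change from baseline (to 6 and 12 months) will be summarised for each of the treatment arms" and continues with "differences between the interventions using unadjusted and adjusted (for age, type of surgery and RT) estimates". Continuous secondary outcomes are to be handled similarly.

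Baseline DASH is not among the named covariates, yet the data exist. Table 3 ticks the primary DASH at 12 months only, but ticks the DASH subscales at baseline. The subscales come from the same questionnaire: "the scale can be used to produce three health outcome subscores for impairment, activity limitation and participation restriction". A change from baseline also presupposes a baseline score.

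Under Sample size, "The study is powered to detect a 7-point difference on the DASH", an effect taken from a small trial "reporting a between-group difference of 7 points on the DASH at 6 months". The result is that "At 80% power and P<0.05, this yields a target of 242 participants in total". This becomes 256 with a design effect of 1.05, and then 350 with an allowance of 25% for loss. The section gives no SD, does not say whether a final or a change score was assumed, and gives no correlation between baseline and follow-up.

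**The concern.** The endpoint is a 12-month score, but the text attaches the treatment contrast to change from baseline and then lists covariates without the baseline score. That is a stated choice, not silence. A change score subtracts the whole baseline value, whatever its actual relation to the 12-month value. A regression on baseline subtracts only as much as the data support. Where the correlation is modest, the change score carries needless noise.

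A modest correlation is plausible here. Most women are randomised before surgery, so their baseline precedes the surgery and adjuvant treatment that drive later disability. Baseline function may also vary widely, because existing shoulder problems are one of several routes to eligibility. Randomisation is stratified by first or repeat surgery, centre and notification of radiotherapy, not by baseline DASH. Neither the design nor the listed covariates therefore remove a chance imbalance in it. At stake are the precision of the primary estimate and, under some assumptions, the stated power.

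**Working it through.** **Inputs from the article (Sample size):** difference 7; power 80%; alpha 0.05; total 242 before inflation; design effect 1.05; 256 after it; 25% loss planned for and under 10% expected; target 350.

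**Assumptions, not in the article:** two-sided test; equal SDs at baseline and 12 months; correlation ρ varied over a range.

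**1. The plan's own figures.** Without an SD, 242 cannot be reproduced, only inverted. With 121 per arm and the normal approximation:

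SD = 7 × √(121/2) / (1.960 + 0.842) = 19.4, a standardised difference of about 0.36.

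The later steps fit approximately: 242 × 1.05 = 254.1 against 256 stated, and 256/0.75 = 342 against 350 stated.

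**2. Relative precision.** In units of the final-score variance:

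- 12-month score alone: 1
- change score: 2(1 − ρ)
- 12-month score adjusted for baseline: 1 − ρ²

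The ratio of change-score to adjusted variance is 2/(1 + ρ), which exceeds 1 for every ρ below 1. It is 1.54, 1.43 and 1.33 at ρ = 0.3, 0.4 and 0.5. The change score is noisier than the unadjusted 12-month score only when ρ is below 0.5.

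**3. Power if 19.4 is a final-score SD.** Effective n per arm is 256/1.05/2 = 121.9, or 315/1.05/2 = 150 with 10% loss from 350. Power = Φ(7 / (SD* × √(2/n)) − 1.960), where SD* is 19.4 times the square root of the factor in step 2.

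| ρ | Change, 256 analysed | Baseline-adjusted, 256 | Change, 315 analysed | Baseline-adjusted, 315 |
|---|---|---|---|---|
| 0.2 | 60% | 82% | 69% | 89% |
| 0.3 | 66% | 84% | 75% | 91% |
| 0.4 | 73% | 87% | 81% | 93% |
| 0.5 | 80% | 90% | 88% | 95% |
| 0.6 | 88% | 94% | 94% | 97% |
| 0.7 | 95% | 98% | 98% | 99% |

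**4. Break-even correlation.** Change scores keep 80% power when 242 × 2(1 − ρ) does not exceed the effective total, so ρ = 1 − (effective total)/484.

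- 256 analysed: 1 − 243.8/484 = 0.50
- 262.5 analysed (25% loss from 350): 1 − 250/484 = 0.48
- 315 analysed (10% loss from 350): 1 − 300/484 = 0.38

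**5. Recruitment needed at ρ = 0.3 with 25% loss.** Change score: 242 × 1.4, rounded up per arm, is 340; × 1.05 = 357; /0.75 = 476. Baseline-adjusted: 242 × 0.91, rounded up per arm, is 222; × 1.05, rounded up, is 234; /0.75 = 312. The target is 350.

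**6. If 19.4 is a change-score SD.** Change-score power is 80% at any ρ. The adjusted analysis has SD 19.4 × √((1 + ρ)/2), which with 256 analysed gives about 94%, 92% and 90% at ρ = 0.3, 0.4 and 0.5. Only this gain is lost.

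**7. Chance imbalance.** With SD 19.4 and 128 per arm, the standard error of the baseline difference is 19.4 × √(2/128) = 2.4 points. An imbalance of that size shifts the change-score estimate by (1 − ρ) × 2.4. At ρ = 0.3 this is 1.7 points, about a quarter of the 7-point target. The unadjusted 12-month comparison shifts by ρ × 2.4 = 0.7 points. Linear adjustment for baseline removes the shift.

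**The case against.** The text can be read more kindly. The regression is said to be of the primary outcome, which is the 12-month score. Change from baseline is *summarised* and then plotted, which could mean display alongside the model. The full model is deferred to a statistical analysis plan that is not shown and that is to be approved before the final analysis. This stands in part: the modelled response is ambiguous, so a reader might infer that baseline DASH will never be a covariate, and the article does not go that far. But the sentence does tie the between-arm estimates to the change scores and names three covariates. A plan that follows it inherits the omission. Not saying whether the unadjusted or the adjusted estimate decides the trial is a detail such a plan may settle, and is not counted against the protocol here.

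The power argument is open to stronger challenge. A reader might infer that the trial is underpowered. The article gives neither the type of SD nor a correlation, so that cannot be concluded. The 25% allowance for loss also leaves slack if loss is below 10% as expected, and persistent pre-existing shoulder problems would tend to raise the correlation. With unequal SDs the point at which change beats the raw 12-month score also moves, to (baseline SD)/(2 × 12-month SD); if the baseline SD were 70% of the later one, that is 0.35.

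Two other strong readings also fail. Change scores are not always the least efficient standard choice, since above a correlation of 0.5 with equal SDs they beat the unadjusted 12-month score. Nor are they biased: under randomisation the comparison is unbiased, and chance imbalance affects only the estimate actually realised.

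**Conclusion.** The concern holds as a matter of precision and clarity, not validity. As described, the between-arm difference is on change from baseline, without baseline DASH in the covariate list, for an endpoint defined at 12 months. With equal SDs this has 33% to 54% more variance than baseline adjustment at correlations of 0.5 down to 0.3, and it leaves more of any chance baseline imbalance in the estimate.

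A shortfall below 80% power is conditional. It requires the implied SD of about 19.4 to be a final-score SD, equal at baseline, and a correlation under about 0.50 with 256 analysed or under about 0.38 with 10% loss. The documents settle none of these conditions. The advantage of adjustment over change scores does not depend on which type of SD was used. This should be fixed before the analysis.

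**What to change.** State in the protocol, and carry into the analysis plan, that the primary model regresses 12-month DASH on arm with baseline DASH added to age, type of surgery and radiotherapy, in multilevel or ordinary form as already planned. Name that adjusted estimate as primary and the unadjusted one as supportive. Keep change from baseline for description and plots. Treat continuous secondary outcomes that have a baseline value in the same way. State the SD behind 242 and whether it refers to final or change scores, so that the power claim can be checked.

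The cost is a few sentences of text. The baseline questionnaire is already collected, so no extra patients, visits or data items are needed.
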